### Participants

The study population will consist of first-degree relatives of patients with premature CHD (males ≤ 55, females ≤ 65), aged 30 years and older. Males and females of Maltese ethnicity seeking cardiovascular risk assessment with no history of cardiovascular disease will be recruited for the study. Other eligibility criteria also apply:
Participants must not have diabetes.Participants must not have a history of rheumatoid arthritis and chronic kidney disease.Participants must not have contraindications against physical activities and can go up a flight of stairs comfortably.Participants must not be pregnant.

### Clinician to deliver the Intervention

The clinician to deliver the Intervention is a qualified nurse who received training from Imperial College London in preventive cardiology ([name]). The clinician has also received training in MI from Sheffield Hallam University. Additionally, the clinician has over 8 years of clinical experience working in the cardiology department.

### Sampling frame

About seven acute coronary syndrome (ACS) patients are admitted to the acute general hospital per week, including unstable angina, non-ST and ST-segment elevation ACS. About 40% will present with premature ACS [4]. Maltese individuals who are 30 years and older often have quite extensive families. Across 52 weeks (1 year), logistically, if every patient informs their relatives, this would amount to over 100 eligible participants. Since there are no records concerning the recruitment uptake and attrition rate, we will dedicate two years for recruitment and data collection. A sample of 100 participants should be adequate to prove that the process is viable. As the pilot study is not expected to be powered to detect differences between groups, there is no universally accepted calculation for the pilot study sample size [38]. If a meaningful group difference is unknown and the pilot study is intended to establish an effect size for sample size calculation, it is recommended to have 30 to 40 participants recruited in each group. Recommendations for feasibility studies propose a minimum of 30 participants per arm to estimate parameters for future sample size calculations [39, 40]. Ultimately, the sample size decision for a pilot RCT must also consider the research timeline, human resources and costs, and the research objectives [40, 41].

### Procedures

#### Recruitment

The flowchart displayed in Fig. 1 summarises the study design and participant flow, from enrolment to the final follow-up. Before discharge, all patients with acute coronary syndrome are enrolled in a hospital-based cardiac rehabilitation program. Patients with premature CHD, who attend cardiac rehabilitation, will be informed by their nurse about the study, which concerns their relatives. Patients will be the source of help to recruit study participants. Poster promotion of the study will be available at the cardiac rehabilitation reception area and local pharmacies. Poster and video clip promoting the study will be shared via the University's social media (Facebook, News point). Those having a sibling or a parent with premature CHD and are seeking cardiovascular risk assessment will be asked to answer a few questions via telephone to assess if they meet the inclusion criteria. Those found to be eligible will be invited for their baseline assessment at the hospital outpatient clinic.

**Fig. 1 Fig1:**
[figure not shown]
Spirit (Standard Protocol Items: Recommendations for Interventional Trials) flow diagram

#### Recruitment method for interviews

All the intervention participants will be asked to complete a questionnaire at the end of the programme.

From a sample of first-degree relatives who completed the programme, 24 individuals will be asked to participate in the interviews. A stratified purposeful sample will be chosen varying on preselected parameters deemed analytically relevant to the Intervention, providing maximum variation. These are sex, age, and risk profile at 12 months. Participants for whom post-intervention outcomes did not improve and participants who had improved their risk profile at 12 months will be purposively selected for focused analysis to identify the Intervention's strengths and weaknesses [32].

#### Group randomisation

Before the baseline/pre-intervention evaluation, approximately 100 participants shall be randomly allocated to one of the two groups:
The intervention group shall consist of 50 participants. Participants in this group will have one face-to-face session (evaluation of modifiable risk factors, 2-way risk factor communication, education, and individualised counselling to set up a cardio-protective documented plan) followed by weekly telephone-based cardio-protective reinforcement sessions for up to 12 weeks.The control group shall consist of 50 participants. Participants will have one face-to-face session of verbal lifestyle advice only.

Block randomisation will be applied to balance out the sample size between the intervention and control groups. An opaque sealed envelope technique, using block randomisation with blocks of size four, will be implemented for this study. This method will allow an equal chance of being allocated to one of the two groups and ensure that near-equal numbers are assigned to each group, minimising the risk of group imbalances and allocation bias.

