#### Blinding and allocation concealment

Awareness of being part of the intervention group may result in participants behaving differently to what they otherwise might do. Group awareness could have implications for the study's internal and external validity. The participants were informed about the aim of the study; however, not about to which group they have been allocated. Furthermore, participants will be allocated by an independent person from the study, and allocation will occur before the baseline/pre-intervention risk evaluation. Due to resource limitations, the study investigator will deliver the Intervention and assess the outcomes, therefore making part of the blinding impossible. However, blinding will be imposed on the data analyst.

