### Ethics

A detailed information letter will be provided to each participant. This letter will explain the nature of the study and what participation would involve. After the participant is given time to clarify anything about study participation, the principal researcher will obtain each participant's consent. It will be made clear that data will be retained in an anonymous form. Participants are free to withdraw at any time during the study. Data will be safely stored in an encrypted computer, and only the principal researcher will have access to this data. This is per data protection directives (GDPR EU 2016/679). The protocol was approved by the University of Malta Ethics Committee (UNIQUE FORM ID: 3756_191119) and the Malta Health Ethics Committee (HEC03 CT01/20).

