### Counterbalancing for confounding factors and bias

There are several possible interacting variables: age, health literacy, educational levels, isolation, employment, sex, psychometric scales, time of the cardiac patient event, and family clustering effects. These multiple variables make it rather complex to decide on stratified sampling. Additionally, as the sample solely depends on the recruitment process, an element that still needs to be tested, it was decided not to stratify at this phase.

The chosen method to generate the allocation sequence should produce comparable groups. However, due to a lack of resources, allocation concealment is not possible. This study is single-blinded, where participants will only be informed about the aim of the study but not about being part of an intervention or control group. However, the researcher will be aware of which participants have been allocated to the intervention group. Thus, there is a risk of performance and detection bias. An independent person from the study will perform group allocation. Also, group allocation will take place before the baseline risk assessment. Using these methods will avoid any attempt to allocate participants to the Intervention according to their risk profile. This step is necessary when the study's nature does not allow proper blinding [56].

Numbers of the total sample randomised, those lost to follow-up, and reasons for withdrawal will be recorded for each group. The risk of attrition bias will be minimised by carrying forward the last observation. This method will keep the groups balanced if there is a loss to follow-up/missed measuring time points.

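### Allocation precedes baseline in fixed blocks of four, the protocol contradicts itself on concealment, and one unblinded researcher takes all measurements, so enrolment and baseline values are open to bias

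*Protocol article*

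**What the plan says.** **Mechanism.** Group randomisation: "An opaque sealed envelope technique, using block randomisation with blocks of size four, will be implemented for this study". The target is 50 per arm, and the counterbalancing section explains that there is no stratification.

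**Order.** Group randomisation: "Before the baseline/pre-intervention evaluation, approximately 100 participants shall be randomly allocated to one of the two groups". Blinding and allocation concealment repeats that "allocation will occur before the baseline/pre-intervention risk evaluation", and gives the task to a person independent of the study. Intervention and control arm then places delivery 2-3 days after the baseline assessment, so that blood results are available.

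**Concealment.** Counterbalancing for confounding factors and bias: "However, due to a lack of resources, allocation concealment is not possible". The same section says that the researcher knows who has been allocated to the intervention. It concedes a risk of performance and detection bias, and presents early allocation as a safeguard against assigning people by their risk profile.

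**Who does what.** Blinding and allocation concealment: "the study investigator will deliver the Intervention and assess the outcomes". Strengths and limitations adds that delivery and all measurements are by the same researcher. Ethics: "the principal researcher will obtain each participant's consent".

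**Eligibility before allocation.** Recruitment: candidates "will be asked to answer a few questions via telephone to assess if they meet the inclusion criteria". Diabetes is an exclusion (Participants), and HbA1c is among the study bloods (biochemical measures, under Secondary outcomes).

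**The concern.** Sealed opaque envelopes held by an independent person are a means of concealing allocation. A statement that concealment is impossible contradicts them, and the reader cannot tell which describes the trial. If there is no concealment, whoever enrols participants could know or foresee the next arm. That is a route to selection bias, which the protocol's list of conceded biases leaves out.

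The order of events adds a second weakness. Because the arm is fixed before baseline, a researcher who has learned it could influence the baseline readings, even without intent. Blood pressure taken by auscultation, waist circumference and questionnaire scores are most exposed; analyser blood results much less. Baseline values matter here because the hypothesis is improvement from baseline, and because baseline balance decides whether variables are adjusted for.

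Third, some events that would best be settled before randomisation may come after it. Undiagnosed diabetes may appear on the baseline HbA1c, or an allocated person may not attend baseline. A non-attender has no observation to carry forward into the intention-to-treat analysis and also affects retention, which is part of the primary feasibility outcome.

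**Working it through.** **1. The plan's own figure.** 100 participants / 4 per block = 25 complete blocks. Each block holds 2 + 2, so 25 × 2 = 50 per arm, as stated. There is no power-based sample size to check.

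**2. The statements on concealment, side by side.**
- Group randomisation: opaque sealed envelopes.
- Blinding and allocation concealment: an independent allocator.
- Counterbalancing section: an independent allocator again, but concealment not possible.

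The first two describe concealment and the third denies it.

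**3. How predictable a fixed block of four is.** Assume that the guesser knows the block size, where blocks start and all past arms, and always guesses the arm with more places left. A 2:2 block has 6 possible sequences.

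| Position in block | Chance that the guess is right | Chance that the arm is certain |
|---|---|---|
| 1 | 1/2 | 0 |
| 2 | 2/3 | 0 |
| 3 | 1/3 × 1 + 2/3 × 1/2 = 2/3 | 1/3 (first two the same) |
| 4 | 1 | 1 |

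- Correct guesses: (1/2 + 2/3 + 2/3 + 1) / 4 = (17/6) / 4 = 17/24 = 70.8%.
- Certain allocations: (0 + 0 + 1/3 + 1) / 4 = 1/3, or about 33.3 of 100.
- Unpredictable allocation would give 50% and none.

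These are upper figures. A researcher who learns an arm only at delivery may not yet know the most recent one when the next person enrols.

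**4. What varied block sizes would change.** Simulation of 3000 trials of 100 participants, with a best guesser who knows the set of possible sizes and all past arms, but not the current block's size:

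| Block sizes | Certain allocations per 100 | Best guess right |
|---|---|---|
| 4 only | 33.3 | 70.8% |
| 4, 6 | 5.5 | 69.2% |
| 2, 4, 6 | 4.1 | 70.1% |
| 4, 6, 8 | 2.4 | 67.9% |

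Varying the size removes most of the certainty but little of the predictability. Real concealment and the timing of allocation matter more.

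**5. Order of events.** The text gives telephone screening, allocation, baseline visit, 2-3 days, delivery. It does not say whether consent comes before allocation, or when the researcher learns the arm. Neither arm's content begins until after the gap, so nothing in the schedule requires the arm to be known at baseline.

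**6. Losses after allocation.** The protocol gives no rate of undiagnosed diabetes and no rate of non-attendance at baseline, so their number cannot be computed. Only non-attenders would lack baseline values; a person whose HbA1c raises a question has attended.

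**The case against.** The strongest reply is that the design already contains safeguards. An independent person allocates from opaque sealed envelopes, and allocating before any risk factor is measured is a deliberate step against steering by risk profile. The protocol openly concedes performance and detection bias. The primary outcomes are feasibility and acceptability, and the pilot is not powered for group differences.

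Much of this stands, and it limits the severity. It does not resolve the contradiction on concealment. Early allocation also does not protect the baseline readings, or enrolment where the next arm can be foreseen. The stated purpose is met equally well by a concealed envelope opened after baseline.

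Two stronger readings are tempting and are not supported:

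- **That the person taking consent knows the allocation scheme.** The text says that the researcher knows arms already allocated, not the coming sequence. Prediction from past arms and the stated block size is possible, but it is an inference. That the principal researcher who takes consent is also the investigator who delivers and assesses is likely, not stated.
- **That ineligible people are being randomised.** Telephone screening precedes the baseline visit, and nothing says that anyone is excluded on baseline HbA1c. The exclusion does not say whether it covers newly detected diabetes, and a condensed article may leave the handling of such cases to the full protocol.

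Knowledge of the arm at baseline is likewise not established. The text only fails to exclude it.

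**Conclusion.** The point holds in a limited form and should be fixed. The contradiction on concealment is plain in the text, as are allocation before baseline, the fixed block size of four, and the single unblinded researcher for delivery and measurement. If that researcher knows the block size and all past arms, up to one allocation in three is certain and up to 70.8% can be guessed correctly. The documents do not show that any prediction takes place, and the resulting bias in the effect estimates cannot be quantified from them.

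The consequence falls mainly on the secondary effect estimates, which may be used to size a definitive trial. The primary feasibility and acceptability results are touched less, through any losses between allocation and baseline.

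**What to change.** For all remaining participants:

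1. The existing independent person holds the envelopes and opens the next one only after consent, confirmed eligibility and completed baseline measurements, within the 2-3 days before delivery. Allocation by risk profile is still prevented, because the sequence is concealed from the researcher who knows that profile.
2. Correct the sentence in the counterbalancing section so that it agrees with Group randomisation and with Blinding and allocation concealment. Separate concealment of the coming allocation, which the envelopes can provide, from blinding of the researcher after allocation, which they cannot.
3. As a supplement only, use randomly varied block sizes that are not disclosed to the investigator.

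**Cost.** A short amendment and a new envelope set. The independent person must be promptly available in each 2-3 day window, which is a real demand given the stated lack of resources. Varied blocks allow slightly more imbalance in arm sizes: a block of four cut short can leave a difference of 2, a block of six a difference of 3, and a block of eight a difference of 4. The new set should start at a block boundary; otherwise a difference of up to 2 from the old set could add to this. Recruitment began in September 2020, so the number of participants who would benefit is not known from the document.

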#### Blinding and allocation concealment

Awareness of being part of the intervention group may result in participants behaving differently to what they otherwise might do. Group awareness could have implications for the study's internal and external validity. The participants were informed about the aim of the study; however, not about to which group they have been allocated. Furthermore, participants will be allocated by an independent person from the study, and allocation will occur before the baseline/pre-intervention risk evaluation. Due to resource limitations, the study investigator will deliver the Intervention and assess the outcomes, therefore making part of the blinding impossible. However, blinding will be imposed on the data analyst.

#### Intervention and control arm

All participants will receive the intervention/control in 2–3 days of completing their baseline/pre-intervention assessment. This period will allow time for blood investigation results to be reported on the electronic health records.

##### Intervention arm

Table 1 shows the intervention content and the behaviour change techniques (BCTs) [42] used in the CRISO intervention. Delivery of the CRISO intervention is personalised to the individuals' specific needs. It allows for flexibility across different participants to maximise support in improving their lifestyle behaviours. This would be achieved through modifiable risk factor evaluation, personalised risk communication, and education using Heart Age. A counselling style approach that draws upon some but not all MI principles and practices will be applied. The participant will be asked to reflect and elaborate on their risk profile. This will include the identification and selection of risk factors that the participant would like to modify. A target goal with specific actions to accomplish will be developed with the clinician's support. Figure 2 provides a central illustration of the program. The algorithm will support first-degree relatives more systematically and equip them with a set of specific actions that they can take to reach the target goal. Table 2 gives a greater focus on the use of specific actions. The clinician will also ask the participant to identify a person who can motivate them to implement specific actions. Reflection on obstacles to change and ways to overcome such challenges are also taken into consideration. Summarising will occur at the end of the session, where the clinician will highlight the target goal and the specific actions selected to reach the goal. This will demonstrate that the clinician was actively listening and listening to understand and not to respond. The clinician will support the participant's strengths to increase their confidence in making change. At the end of the session, an electronic preventive cardiology report (Table 3) will be forwarded to the participant. The report will include a cardioprotective plan developed by the participant and the clinician through discussion. The report is to be updated for the participant at 6 months and 12 months follow-up (Table 3).

**Table 1 Tab1:**
[figure not shown]
Content summary for the CRISO intervention and BCTs

**Fig. 2 Fig2:**
[figure not shown]
CRISO intervention programme algorithm

**Table 2 Tab2:**
[figure not shown]
Intervention risk factor and behavioural targets

**Table 3 Tab3:**
[figure not shown]
Preventive cardiology report template

**Table 4 Tab4:**
[figure not shown]
Data collection points

✓* Intervention delivered 2-3 days after T0 for blood results to be issued

✓** Control delivered 2-3 days after T0 for blood results to be issued

Telephone reinforcement sessions following the combined risk communication and counselling session will also be used. In total, participants receive one in-person session and 12 telephone calls (occurring between weeks 1 and 12).

##### Theoretical model

The chosen theoretical model of behaviour change is the Capability Opportunity Motivation–Behaviour model (COM-B). Other theoretical frameworks, such as the behavioural choice theory or theory of planned behaviour, social cognitive theory, and self-regulation theory, appeared ineffective in similar studies [29]. The behaviour change wheel is a theoretical framework that led to the development of the COM-B model. The COM-B is a simple, cost-effective model to apply to all behaviours [43–45]. The model is pivotal in simplifying how behaviours could be targeted [46] and aids in supporting change in one or more of the following: capability, opportunity, and motivation relating to the behaviour itself or behaviours that compete with or support it. Drafting the programme using the COM-B model allowed for insights into how the programme intervention could alter risky behaviours. The COM-B model theory states that there must be the ‘capability’ for modification to modify behaviour (sedentary lifestyle, unhealthy dietary eating patterns, and smoking). First-degree relatives must have the physical and psychological capability to modify risk by developing knowledge through professional contact, discussing risk via visual aids, and discussing risk-reduction methods through the provision of feedback and monitoring. The CRISO program may facilitate an environment for opportunistic screening, improve professional contact, and encourage first-degree relatives to seek risk assessment. The Heart Age risk calculator was identified to educate about, evaluate, and communicate risk to increase understanding of risk and support participants to act on it. In return, this should improve understanding of risk and enhance the capability and opportunity to modify risk factors. Using a counselling style adapted from MI might further support individuals in identifying and select behaviours that require modification [29].

##### Control arm

About 70% of general practitioners' CVD risk consultations happen in verbal terminology [47]; participants assigned to the control arm will only receive one in-person session based on verbal lifestyle advice, referring to the European Society of Cardiology lifestyle targets about smoking, dietary pattern, and physical activity levels [3].

